## Introduction

1

Work stress refers to a phenomenon in which personal factors and the workplace environment interact to negatively affect workers’ physical and psychological functions (1). Previous studies have shown that chronic stress at work can lead to physical illness and psychological disorders (2, 3). Work stress has a negative impact not only on an individual’s health but also on their attitude and performance toward their job. Work engagement refers to a state in which they highly identify with their job and are highly physically, cognitively, and emotionally involved in their job (4). Burnout, the opposite state of work engagement, appears as a response to chronic emotional and interpersonal stressors at work and results in exhaustion, cynicism, and lack of efficacy (5). In this way, chronic work stress could cause negative perceptions of the job and further worsen job performance. Indeed, previous studies have shown that excessive work-related stress reduces personal health and work motivation, increases mistakes and accidents, and ultimately reduces organizational efficiency and productivity (6, 7). According to other studies, work stress causes general health problems, increases burnout, and reduces job satisfaction and work engagement (8–10). For this reason, interest in methods for managing work stress is increasing. Common interventions for managing workers’ stress include mind–body interventions such as mindfulness and relaxation techniques (11).

Recently, various mobile healthcare applications have been developed for mental health management (12). Mobile-based interventions can deliver high-quality education without geographical and economic constraints and can provide customized education suitable for individuals (13). Furthermore, because these interventions are easy to standardize, they may be as effective in improving health outcomes as well-designed offline education (13). According to previous studies, mobile healthcare applications can reduce psychological symptoms, prevent disease, and improve wellbeing (14–16).

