The secondary objective of this study is to perform a follow-up examination to assess the effect of MMT on the mental health, stress, burnout, and work engagement of employees over a longer period. The results of this study are predicted as follows: (i) Burnout at follow-up will be lower than that at baseline in the experimental group. (ii) Work engagement at follow-up will be higher than that at baseline in the experimental group. (iii) Perceived stress at follow-up will be lower than that at baseline in the experimental group. (iv) Mindfulness at follow-up will be higher than that at baseline in the experimental group. (v) Subjective vitality at follow-up will be higher than that at baseline in the experimental group.

The third objective of this study is to examine differences in the effectiveness of MMT depending on the amount of application usage. The results of this study are predicted as follows: (i) The high-usage subgroup will exhibit a greater reduction in burnout compared to the low-usage subgroup after MMT. (ii) The high-usage subgroup will exhibit a greater increase in work engagement compared to the low-usage subgroup after MMT. (iii) The high-usage subgroup will exhibit a greater reduction in perceived stress compared to the low-usage subgroup after MMT. (iv) The high-usage subgroup will exhibit a greater increase in mindfulness compared to the low-usage subgroup after MMT. (v) The high-usage subgroup will exhibit a greater increase in subjective vitality compared to the low-usage subgroup after MMT.

The fourth objective of this study is to examine whether mindfulness and subjective vitality mediate the relationship between MMT and burnout or work engagement. The results of this study are predicted as follows: (i) Mindfulness will mediate the relationship between MMT and burnout. (ii) Mindfulness will mediate the relationship between MMT and work engagement. (iii) Subjective vitality will mediate the relationship between MMT and burnout. (iv) Subjective vitality will mediate the relationship between MMT and work engagement.

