#### Maslach burnout inventory—general survey (MBI-GS)

2.10.1

The Korean version of the MBI-GS will be used to assess burnout (36). This scale consists of 5 items for burnout, 4 items for cynicism, and 6 items for decreased job efficacy. Decreased job efficacy is reverse scored. The MBI-GS is a self-reported 5-point Likert scale. Each item ranges from 1 to 5. The total score ranges from 15 to 75. A higher score indicates more severe burnout. In a previous study (36), Cronbach’s alpha was 0.90 for burnout, 0.81 for cynicism, and 0.86 for decreased job efficacy.

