#### The Utrecht work engagement scale (UWES)

2.10.2

The Korean version of the UWES will be used to assess work engagement (37). This scale consists of 3 items for vigor, 3 items for dedication, and 3 items for absorption. The UWES scale is a self-reported 7-point Likert scale. Each item ranges from 0 to 6. The total score ranges from 0 to 54. A higher score indicates more immersion in one’s job. In previous studies (37), Cronbach’s alpha was 0.91 for vigor, 0.89 for dedication, and 0.90 for absorption.

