#### Integrative vitality scale (IVS)

2.11.3

The IVS is a self-report scale that measures physical and psychological vitality (40). The scale consists of 22 items, 11 items for physical vitality and 11 items for psychological vitality. The IVS is a self-report 5-point Likert scale. The total score ranges from 0 to 44 for physical vitality and from 0 to 44 for psychological vitality. One item (e.g., My head feels heavy and achy) is reverse scored. Higher scores indicate higher physical and psychological vitality. In a survey of 348 people, Cronbach’s alpha was 0.91 for physical vitality, 0.91 for psychological vitality, and 0.94 overall (40).

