### Statistical analyses

2.13

Analyses will be conducted according to the Intention-To-Treat (ITT) principle, and missing data will be imputed using the expectation maximization algorithm.

First, to investigate the effectiveness of MMT, a 2 (group: experimental vs. control) × 2 (survey time: T1 vs. T2) repeated-measures ANOVA will be performed for MBI-GS, UWES, PSS, CMAS-R, and IVS. If the interaction between the group and survey time is significant, a simple main effect analysis will be performed. Second, a paired *t-*test will be performed on MBI-GS, UWES, PSS, CMAS-R, and IVS in the experimental group to examine the follow-up effect of MMT. Third, a subgroup analysis will be performed to investigate the difference in effectiveness depending on the amount of application usage. For this purpose, 2 (subgroup: high-usage vs. low-usage) × 2 (survey time: baseline vs. post-intervention) repeated-measures ANOVA will be performed. Data from both the experimental and control groups will be used for subgroup analysis. If the interaction between the subgroup and survey time is significant, a simple main effect analysis will be performed. Fourth, a mediating effect analysis will be performed to investigate whether mindfulness and subjective vitality mediate the relationship between application use and burnout or work engagement.

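### The vitality mediator overlaps by label with the vigor third of UWES, and possibly with the first MBI-GS subscale, so a mediation found only on the total scores could not be read as a mechanism

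*Protocol article*

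**What the plan says.** The Introduction sets two vitality hypotheses under the fourth objective: "Subjective vitality will mediate the relationship between MMT and burnout", and "Subjective vitality will mediate the relationship between MMT and work engagement". Section 2.13 plans the matching test in one sentence: "a mediating effect analysis will be performed to investigate whether mindfulness and subjective vitality mediate the relationship between application use and burnout or work engagement".

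The instruments are described as follows.

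- **Mediator (section 2.11.3):** "The IVS is a self-report scale that measures physical and psychological vitality". It has 22 items, 11 physical and 11 psychological. One item is shown, and it is somatic (a heavy, aching head).
- **Engagement (section 2.10.2):** "This scale consists of 3 items for vigor, 3 items for dedication, and 3 items for absorption". The score is a total from 0 to 54.
- **Burnout (section 2.10.1):** "This scale consists of 5 items for burnout, 4 items for cynicism, and 6 items for decreased job efficacy". The score is a total from 15 to 75. The Introduction says that burnout "results in exhaustion, cynicism, and lack of efficacy".

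Section 2.9 has all three scales self-reported at the same three time points. The Discussion expects the mediator analysis to allow psychological mechanisms to be verified and applied to other interventions.

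**The concern.** By the article's own labels, a vitality scale is used to explain a total of which one third is vigor. For burnout the parallel takes one more step. The second and third MBI-GS subscales match the cynicism and efficacy components named in the Introduction, so the remaining 5-item subscale probably corresponds to exhaustion, although section 2.10.1 labels it burnout.

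Where mediator and outcome share content, the mediator-to-outcome path (path b) can be significant because energy is scored on both sides. If MMT also raises vitality (path a), the analysis reports mediation even when vitality does nothing for dedication, absorption, cynicism or efficacy. Measuring vitality earlier than the outcome would not remove the shared content. What is at stake is the reading of hypotheses (iii) and (iv) of the fourth objective as evidence of a mechanism.

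**Working it through.** **1. The trial sizes.** Section 2.6 gives an effect size of 0.15, alpha 0.05, power 0.80, N = 90, and 114 after 20% dropout. For a repeated-measures within-between interaction with 2 groups and m = 2 times, reading 0.15 as Cohen's f and assuming a correlation ρ = 0.5 between times, λ = f²·N·m/(1−ρ) = 0.0225 × 90 × 2 / 0.5 = 8.1. This gives power 0.804, so 90 reproduces. Per arm, 45/0.8 = 56.25, rounded up to 57, or 114 in total, as stated. Both sizes are used below.

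**2. How much of each outcome can overlap.** UWES: 3/9 = 33%. MBI-GS: 5/15 = 33%. Two thirds of each total cannot be affected.

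**3. The simulation model.** Let x be the randomised arm and d the effect of MMT on vitality in SD units.

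- Latent vitality: E = d·x + noise.
- IVS: M = √0.94·E + √0.06·noise, with 0.94 the overall alpha in section 2.11.3.
- Overlapping subscale: V = r·E + √(1−r²)·noise, with r the overlap.
- Rest of the outcome, R: no link to x or E.
- Total: Y = V/3 + 2R/3.

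Mediation is declared when path a (M on x) and path b (Y on M, adjusted for x) both have p < 0.05. The values of d and r are assumptions, because the article gives neither.

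**4. Results at N = 90** (2,000 trials per cell; share of trials declaring mediation):

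| d | r = 0 | r = 0.3 | r = 0.5 | r = 0.7 | r = 0.9 |
|---|---|---|---|---|---|
| 0 | 0.1% | 1% | 2% | 4% | 5% |
| 0.3 | 1.5% | 7% | 16% | 22% | 26% |
| 0.5 | 3.3% | 15% | 32% | 52% | 61% |
| 0.8 | 5.0% | 21% | 51% | 80% | 93% |

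A further run with r from 0.3 to 1.0 and d from 0.3 to 0.6 gave about 7% to 78% at N = 90 and 11% to 88% at N = 114. The ends move by a point or two with simulation error and with how the remaining subscales are modelled.

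**5. Why the figures come out this way.** The declared rate is roughly P(path a significant) × P(path b significant).

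- No effect on vitality: at most 0.05 × 1 = 5%.
- Full overlap: path b is almost always significant, so the rate is the power of path a. With d = 0.6 × √0.94 = 0.58, a two-sample t-test has power 0.78 at 45 per arm and 0.87 at 57 per arm, which is the upper end of the range.
- Overlapping items removed: 0.05 × 0.78 = 3.9% and 0.05 × 0.87 = 4.4%, or about 4%.

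**The case against.** **The degree of overlap is not documented.** A reader might infer that IVS largely re-measures vigor and exhaustion. The article does not support that. It shows one of 22 IVS items, half the scale is physical vitality, and it gives no correlation between IVS and either outcome. A general vitality scale and a work-engagement subscale may be related without being the same variable. This stands, and it limits the point to conceptual overlap by label. For MBI-GS even the label has to be inferred.

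**Overlap alone is not enough.** A reader might also infer that shared content produces mediation by itself. It does not: unless MMT changes vitality, the rate stays at or below about 5%. This stands too, although the primary objective predicts such a change.

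**The simulation returns what is put into it.** The highest rates are in effect the power to detect MMT's effect on vitality, and the low rate after removal follows from giving the rest of the outcome no link to vitality. That is fair. A single figure near 80% would therefore mislead, and only the range is informative. It still shows that overlap confined to one third of a total can carry the result.

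**Dropping the items changes the hypothesis.** The hypotheses concern engagement and burnout as a whole, and a real mechanism acting through vigor would be lost. This stands against replacing the outcome, but not against adding a companion analysis.

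**The detail may sit in a full protocol or analysis plan not shown.** It may. The point therefore rests on what the article does fix: the mediator, the scored totals, and the intended reading as a verified mechanism.

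**Conclusion.** The point holds as a limit on interpretation. The article's labels put vitality on the mediator side and vigor inside the engagement total; for burnout the parallel is possible but inferred. If MMT changes vitality by 0.3 to 0.6 SD and the overlap correlation is 0.3 to 1.0, the planned total-score test declares mediation in about 7% to 78% of trials at N = 90 and 11% to 88% at N = 114 when vitality has no link to the remaining two thirds of the outcome. The rate is at most about 4% once the overlapping items are removed.

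These rates rest on assumed d and r, on a remainder unrelated to vitality, and on randomised arm as the exposure; section 2.13 names application use. It would go too far to conclude that a positive vitality result must be an artefact, or that the trial's main findings are in doubt. The 2 × 2 group-by-time comparisons and the sample size do not depend on the mediation analysis.

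**What to change.** In section 2.13, keep the total-score mediation and add, for vitality only, a pre-stated companion analysis with two reduced outcomes:

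- UWES without vigor: dedication + absorption, 3 + 3 = 6 items.
- MBI-GS without its first 5-item subscale: cynicism + decreased job efficacy, 4 + 6 = 10 items.

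State the reading in advance. If mediation appears only on the totals, report that it cannot be told apart from shared content, and do not describe vitality as a verified mechanism for engagement or burnout as a whole.

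The cost is a sentence or two in the plan and a second scoring of data already being collected. Section 3.1 says that recruitment has not started, so the rule can be set before any data exist. The downside is that the reduced scores have fewer items, probably slightly lower reliability, and cover less of each construct, which is why they accompany the totals and do not replace them.

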For event guidelines, whenever participants experience stress during their daily or work life, they will be asked to practice meditation or listen to healing sounds recommended for that stressful situation. A total of four types of stressful situations are listed, namely, acute work stress, chronic work stress, interpersonal stress, and daily life stress. In acute-stress situations, concentrative meditation and healing sounds will be recommended for quick relaxation. In chronic stress situations, mindfulness meditation and healing sounds will be recommended for emotional regulation. In situations of interpersonal stress, compassion meditation and healing sounds will be recommended to improve interpersonal relationships. In situations of daily life stress, meditation that is easy to apply in daily life (e.g., meditation for deep sleep, morning meditation for a special day) and healing sounds will be recommended. Participants will be asked to autonomously perform the recommended content for the relevant stressful situation. Education on daily and event guidelines will be provided to improve compliance with the intervention protocol.

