## Discussion

3

This study aims to investigate the effects of MMT on office workers. This study is designed as a two-armed randomized controlled trial and will primarily investigate the effects of MMT on perceived stress, burnout, work engagement, mindfulness, and subjective vitality. Additionally, this study will investigate the follow-up effect of MMT and perform subgroup analysis to compare differences in effectiveness depending on application usage. Finally, this study will investigate whether mindfulness and subjective vitality mediate the relationship between MMT and burnout or work engagement.

MMT will improve the mental health and productivity of office workers. According to previous studies, mindfulness training reduced perceived stress (16) and increased mindfulness and subjective vitality (41, 42). Mindfulness training reduced job burnout and increased job engagement among health care providers (25, 43). Furthermore, the positive effects of MMT will be maintained even after completing the intervention. According to a meta-analysis study, the follow-up effect of mindfulness meditation on anxiety and stress was found to be significant (16). These results suggest that MMT improves the mental health and productivity of office workers, and that the improved effects can be maintained even after training ends.

The amount of application usage will affect the effectiveness of MMT. According to previous research, as the number of sessions of mindfulness training increased, stress significantly decreased (44). According to a study that examined the effects of mindfulness training on a weekly basis (45), the level of mindfulness significantly increased after 2 weeks of training, and perceived stress significantly decreased after 4 weeks of training. These findings suggest that the effectiveness of MMT may also increase as the amount of application usage increases.

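### The mediation hypotheses concern MMT, but section 2.13 names application use as the exposure, and usage as that paragraph employs the term is not randomised

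*Protocol article*

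**What the plan says.** The Introduction gives the fourth objective as to "examine whether mindfulness and subjective vitality mediate the relationship between MMT and burnout or work engagement". Its four hypotheses all take MMT as the exposure; the first reads "Mindfulness will mediate the relationship between MMT and burnout". The Discussion (section 3) repeats that the study will "investigate whether mindfulness and subjective vitality mediate the relationship between MMT and burnout or work engagement".

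Section 2.13 plans one analysis for this objective, to examine "whether mindfulness and subjective vitality mediate the relationship between application use and burnout or work engagement". It does not define application use.

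The third analysis in the same paragraph gives the nearest context: "a subgroup analysis will be performed to investigate the difference in effectiveness depending on the amount of application usage". There, usage is split into high and low, and "Data from both the experimental and control groups will be used for subgroup analysis". When that paragraph refers to the randomised comparison, it calls it group, experimental versus control.

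Only group is randomised (section 2.7). How much a participant uses the app is largely self-directed. For the event guidelines in section 2.4.1, "Participants will be asked to autonomously perform the recommended content for the relevant stressful situation"; the daily sessions are requested, not supervised.

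**The concern.** The exposure in the analysis is not the exposure in the hypotheses. If application use means amount of use, the planned model asks whether heavier users change more in mindfulness or vitality, and whether that goes with less burnout or more engagement. That is an observational dose-response question. The objective asks about the effect of being given MMT.

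Motivation or workload could drive use, mindfulness and burnout together. Motivated workers who would have improved anyway would then look like evidence of a mechanism. All outcomes are self-reported (section 2.9) and participants are unblinded (section 2.8), which makes a shared influence on mediator and outcome more plausible. The Discussion hopes that mechanisms can be verified and carried into other interventions, so the claim at stake is causal. As written, the four hypotheses may have no matching test.

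**Working it through.** **Step 1: the texts side by side**

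| Place | Exposure named |
|---|---|
| Introduction, fourth objective | MMT |
| Introduction, its hypotheses (i) to (iv) | MMT |
| Discussion, section 3 | MMT |
| Section 2.13, fourth analysis | application use |

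This mismatch depends on no calculation.

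**Step 2: the plan's figures.** The article gives no figure for the mediation analysis. Its sample size (section 2.6) serves here only as n: 45/0.8 = 56.25, rounded up to 57 per group, so 114 recruited and 90 after the planned dropout. That agrees with the article.

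**Step 3: how far amount of use could mislead.** All inputs other than n are assumptions:

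- The app affects nothing, and the mediator does not affect the outcome.
- One trait correlates ρ with use, with mediator change and with outcome change.
- Use is continuous and observed in all 114 participants, pooling both arms over their own MMT periods.
- Mediation is declared when both paths have p < 0.05.

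The use-mediator correlation is ρ². The mediator-outcome correlation given use is (ρ² − ρ⁴)/(1 − ρ⁴) = ρ²/(1 + ρ²). For a correlation r, the expected statistic is about t = r√df/√(1 − r²), with df = 112 for path 1 and 111 for path 2. The chance of significance is about Φ(t − 1.98) + Φ(−t − 1.98). The product treats the two tests as independent.

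| ρ | Path 1: r, t, chance | Path 2: r, t, chance | Product | Simulated |
|---|---|---|---|---|
| 0.3 | 0.09, 0.96, 0.15 | 0.083, 0.87, 0.14 | 0.02 | 2% |
| 0.4 | 0.16, 1.72, 0.40 | 0.138, 1.47, 0.30 | 0.12 | 11–13% |
| 0.5 | 0.25, 2.73, 0.77 | 0.200, 2.15, 0.57 | 0.44 | 42–44% |

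**Step 4: sensitivity**

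- At ρ = 0.5 the rate falls to about 32% with n = 90 and about 14–15% with n = 57 (one arm only).
- If both arms are analysed over T1 to T2 with control use entered as zero, it is about 9–22% at ρ = 0.5 and 4–6% at ρ = 0.4 (n = 114), depending on the assumed mean use.
- If the mediator does affect the outcome (coefficient −0.4) while the app still has no effect, it is higher: about 14%, 32% and 67% at trait loadings of 0.3, 0.4 and 0.5 with n = 90.

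**Step 5: what naming group does and does not repair.** Take randomised group as the exposure, n = 114, the same trait (ρ = 0.5) on mediator and outcome, and no effect of mediator on outcome. Given group, the mediator-outcome correlation is 0.25, so t = 0.25√111/√0.9375 = 2.72 and the chance is 0.77. If MMT shifts the mediator by d standard deviations, path 1 has t = d/√(2/57) = d/0.187.

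| d | Path 1 t | Path 1 chance | × 0.77 | Simulated |
|---|---|---|---|---|
| 0 | 0 | 0.05 | 0.04 | about 4% |
| 0.3 | 1.60 | 0.35 | 0.27 | 26% |
| 0.5 | 2.67 | 0.75 | 0.58 | 59% |
| 0.8 | 4.27 | 0.99 | 0.76 | 77% |

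The low rate holds only if MMT leaves the mediator unchanged, and the first objective predicts that it will raise mindfulness.

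**The case against.** **The term may be loose wording.** MMT in this trial is being given the app. The fourth analysis says application use, whereas the third speaks of the amount of usage. The Discussion restates the question with MMT, section 2.13 opens with the intention-to-treat principle, and pooling of the arms is stated for the subgroup analysis only. This stands as far as it goes. A reader might infer that the plan has definitely swapped the randomised arm for self-selected use; the documents do not establish that, because the term is undefined. The neighbouring sentences make amount of use the more likely reading. On either reading the sentence must be corrected, since it leaves the analyst free to choose the exposure.

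**The fix does not secure the mechanism claim.** This also stands. A reader might set the 44% for use against about 4% for the randomised arm and conclude that naming group removes the problem. Step 5 shows otherwise: under the same mediator-outcome confounding, the group-based analysis also declares false mediation often once MMT moves the mediator. Randomisation protects the paths from group and nothing further along.

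**The illustration depends on its inputs.** The article gives no correlation between use, mediator and outcome. At 0.3 in the base model there is no inflation above 5%. The 44% should not be read as a forecast.

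**The consequence is limited.** This is the fourth objective. No primary comparison, sample size or participant procedure is affected.

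**Conclusion.** The inconsistency is real and rests on the current text: the hypotheses name MMT and the only analysis planned for them names application use. If that means amount of use, the analysis answers a different question, and the exposure-mediator and exposure-outcome paths are no longer protected by randomisation. If it means assignment, the sentence is a wording error that still has to be corrected.

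The possible size is false joint significance of about 2%, 12% and 44% at trait correlations of 0.3, 0.4 and 0.5. This assumes no effect of the app, a single shared trait and continuous use observed in all 114; smaller n gives lower rates. These figures show only that the problem can be material. They do not show that the group-based analysis is safe. The point should be corrected before recruitment, but it does not touch the main comparisons.

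**What to change.** In section 2.13, replace the sentence on the fourth analysis with wording such as:

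> For the fourth objective the exposure is randomised group (MMT versus wait-list) over T1 to T2. The mediators are CAMS-R and IVS and the outcomes MBI-GS and UWES, all at T2, with adjustment for the T1 value of the mediator and of the outcome. Any mediation analysis based on amount of use is supplementary and observational. Randomisation protects only the paths from group. The mediator-outcome path is not randomised and both are measured at T2, so unmeasured confounding of that path and an assumed time order limit any conclusion about mechanism.

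The method for the indirect-effect interval can be left to the statistical analysis plan. The Introduction and Discussion need no change to their statement of the objective.

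The cost is a few sentences in one section, with the same data, visits and sample size. Section 3.1 says recruitment has not started, so the change can still be made in advance.
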